# SINFONIA study protocol: a phase II/III randomised controlled trial examining benefits of guided online group singing in people with chronic obstructive pulmonary disease and interstitial lung disease and their carers

**DOI:** 10.1186/s12931-022-02133-3

**Published:** 2022-08-16

**Keywords:** Chronic obstructive pulmonary disease, Interstitial lung disease, Advanced lung disease, Breathlessness, Community, Intervention, Singing, Music therapy, Online

## Abstract

**Background:**

Chronic obstructive pulmonary disease (COPD) and interstital lung disease (ILD) are incurable conditions characterised by airflow limitation, persisting respiratory symptoms, and progressive respiratory failure. People living with COPD or ILD often suffer from chronic and severe breathlessness, with limited treatment options and low engagement rates with current therapies. Group singing represents a potential community-based therapy to improve quality of life for patients with COPD or ILD and breathlessness.

**Methods:**

This protocol papers describes SINFONIA, a parallel, double-arm, randomised, blinded-analysis, mixed-methods phase II/III trial of guided, online group singing that will be conducted over 24 months. Adults with confirmed COPD or ILD, on stable treatment for at least four weeks at time of recruitment, with a modified Medical Research Council (mMRC) dyspnoea score of two or greater, who are capable and willing to give consent, and not currently participating in pulmonary rehabilitation will be eligible to participate. Carers may optionally enrol in the trial. Data will be collected on quality of life, anxiety and depression, breathlessness, mastery of breathing, exercise tolerance, loneliness, healthcare utilisation, and carer quality of life (optional). Participants will be randomised 1:1 to intervention or control arms with intervention arm attending one 90 min, guided, online, group singing session per week for 12 weeks and control arm continuing routine care. Phase II of the trial aims to determine the feasibility and acceptability of guided, online group singing and will collect preliminary data on effectiveness. Phase III aims to determine whether guided, online group singing has an effect on quality of life with the primary outcome being a between arm difference in quality of life (36-item Short Form Survey) measured at 12 weeks.

**Discussion:**

SINFONIA is the first study is the first of its kind in Australia and to our knowledge, the first to deliver the singing intervention program entirely online. Determining the feasibility, acceptability, and effectiveness of guided, online group singing is an important step towards improving low-cost, low-risk, community-based therapeutic options for patients living with COPD or ILD and breathlessness.

*Trial registration:* Phase II—ACTRN12621001274864, registered 20th September 2021; Phase III—ACTRN12621001280897, registered 22nd September 2021.

## Background

Chronic obstructive pulmonary disease (COPD) is an incurable condition characterised by airflow limitation, persisting respiratory symptoms, and progressive respiratory failure [1]. In Australia, COPD represents 43% of all chronic respiratory disease burden [2], affecting 30% of people aged over 75 years [3], with disproportionate impacts on those living in regional areas or with lower socioeconomic status [4]. With over 72,000 admissions each year attributable to COPD, it is the third leading cause of avoidable hospitalisation and generates significant healthcare costs [5, 6]. Internationally, COPD is the second most common respiratory disease after asthma in the United Kingdom [7] and the third leading cause of death worldwide [8]. Interstitial lung disease (ILD) is an umbrella term which captures a large group of diseases resulting in fibrosis of the lungs [9], which often generate distressing, progressive symptoms, and account for a further 8% of chronic respiratory disease burden in Australia [2].

Breathlessness is *“a subjective experience of breathing discomfort that consists of qualitatively distinct sensations that vary in intensity”* which derive from a complex interaction of physiological, psychological, and environmental factors [10]. It is the most common symptom in people with advanced lung disease (ALD), including COPD [11] and ILD [12], and is notoriously difficult to treat [13, 14]. Breathlessness is frequently associated with depression, anxiety, loss of function, social isolation and reduced quality of life [15–17]. Additionally, the presence of breathlessness is a predictor of unscheduled healthcare use, hospitalisation and mortality in patients with ALD [18, 19].

Pulmonary rehabilitation (PR) is a well-established, holistic, therapeutic program encompassing tailored exercise, breath training, psychosocial counselling, and patient education, which has been shown to improve symptoms and function, and reduce hospitalisations [20]. Despite these benefits, referral to, and completion of, PR programs in patients with ALD is alarmingly low [21]. Of the nearly 1.5 million older Australians living with symptomatic COPD, fewer than 10% have ever accessed a program [22]; and internationally fewer than 3% have accessed pulmonary rehabilitation after hospitalisation for an exacerbation of their disease [23]. Participation rates for people with ILD are not well documented. Common barriers to participating in PR include: poor understanding of the program by health professionals and patients, complicated referral pathways, challenges travelling long distances or attending in person (due to symptoms or lack of social support) [24], and limited availaibility of in-person programs in many areas (which has been exacerbated by the COVID-19 pandemic) [23]. Given these challenges, there is a need for sustainable, novel, community-based interventions that are acceptable to patients and their carers, and effective in reducing symptom burden.

Singing is a low-cost, low-risk activity that is recommended for a range of health conditions including neurological [25], mental health [26], and respiratory disorders [27]. Singing can be delivered as a guided, weekly, group-based activity, emphasising focus and control of breathing for patients with ALD. Trials of guided, group singing as a respiratory health intervention have been conducted in New Zealand [28], China [29], Brazil [30], and the United Kingdom [31–33]. Although evidence of robust physiological benefits is mixed [30, 34, 35], studies report improvements to anxiety and depression [28, 29, 33, 35], exercise tolerance [28], and overall quality of life [29–32, 35]. These trials are frequently limited by low study numbers and high risk of bias [27, 36]. To date there are no trials of singing as a therapeutic intervention for ALD in Australia, or in patients with ILD internationally. Robust and long-term studies in the Australian context and in different disease groups are necessary to determine the acceptability and healthcare cost–benefit of guided, group singing for patients with ALD.

Restrictions imposed by the COVID-19 pandemic limit the feasibility of face-to-face singing groups given the aerosol generating nature of singing, and raise the question of whether guided, group singing can offer the same benefits when the intervention is delivered entirely online. Nevertheless, online delivery represents an attractive opportunity to improve healthcare access for participants with limited mobility, poor health, or who live in a rural location with limited access to health services. This is particularly relevant in Australia, where a third of the population lives in regional or remote areas with reduced service availability [37] despite chronic respiratory disease being overrepresented amongst this group [38]. The SINFONIA study (a clinical trial examining the benefits of **S**ing**IN**g **F**or breathing in C**O**PD a**N**d **I**LD p**A**tients) aims to determine the feasibility, acceptability, and effectiveness of guided, online, group singing as an intervention to improve quality of life in patients with COPD or ILD with significant breathlessness living in Australia.

## Methods

### Study design and setting

A parallel, double-arm, randomised, blinded-analysis, mixed-methods phase II/III trial of guided, online group singing will be conducted over 24 months. Adults with COPD or ILD and their adult carers (optional) will be eligible to participate. Methods reported in this paper are reflective of protocol version 1.2, 30^th^ September 2021. Participants will be recruited from tertiary respiratory care clinics based at the Alfred Hospital, Austin Health, Royal Melbourne Hospital, and St Vincent’s Hospital in Melbourne, Australia. People who are not cared for by these health services may also be referred to the study by their primary care provider (e.g., general practitioner) or by self-referral. An advertising poster with eligibility criteria and contact details will be circulated amongst specialist and community pulmonary care services to enable referral. All referred patients will be reviewed by an investigator at a study site to confirm eligbility. Ethics approval for the study was obtained from the St Vincent’ Hospital Melbourne Human Research and Ethics Committee (LRR 237/21).

### Participants

Adults with confirmed COPD or ILD, on stable treatment for at least four weeks at time of recruitment, with a modified Medical Research Council (mMRC) dyspnoea score of two or greater, who are capable and willing to give consent, are eligible to participate. Diagnosis of COPD or ILD must be confirmed by lung function testing within the past two years or computed tomography (CT) chest scan within the past five years. Stable treatment is defined as no new or altered doses of cardiorespiratory medications (including antibiotics and oral steroids) as assessed by the study site clinician, and no hospital admissions for exacerbation of their underlying disease within the past four weeks. Participants who are actively enrolled in a PR program are excluded from participation; however past completion is permitted. No other exclusion criteria exist. A nominated carer (aged 18 years or over) per participant may optionally be enrolled. Referral of participants who are not patients of the study site clinics is permitted. Informed written consent will be obtained by an appropriately trained member of the study team.

### Intervention and data collection

Participants and their carers (optional) will be enrolled for a period of 12-weeks (Fig. 1). After signing consent, participants will be randomised 1:1 to intervention or control arms with the randomisation sequence developed by the trial statistician using permuted block design (Stata statistical package [39]), and stratified by disease type (ILD vs COPD). Allocation sequence will not be visible to personnel involved in study recruitment. Participants randomised to the intervention arm will attend one 90-minute, guided, online, group singing session per week for 12 weeks. Enrollment will be on a rolling basis with a maximum of 12 patient participants and 12 carers, with up to two groups running concurrently.

**Fig. 1 Fig1:**
[figure not shown]
Study diagram

The online program will be delivered via a teleconferencing platform such as Zoom. Online, group singing sessions will be conducted by a senior music therapist with expertise in singing and delivering an individualised, enjoyable singing repertoire suitable for patients with ALD (Table 1). Singing activities will focus on breathing control and will include a warm-up. Participants will be encouraged to suggest songs. During the 90 minute class, some time will be dedicated to socialisation and group connection. The exact content and structure of the online group singing sessions will be refined during phase II.

**Table 1 Tab1:** SINFONIA music therapy session plan

Stage	Content	Time
Welcome and check in	•Check and provide support for technical issues •Briefly assess participants for comfort level •Identify any issues for consideration during session	5 min
Relaxation	•Relaxation exercise to support comfort and set expectations	5 min
Warm up	•Revision of techniques •Application of techniques to previous session	15 min
Main session (part I)	•Education, practice, and application of targeted breathing and singing techniques	25 min
Break	•Comfort break for bathroom or refreshments	5 min
Main session (part II)	•Application of targeted singing and breathing techniques to participants preferred repertoire	30 min
Reflection	•Reflection on content of session •Suggestions for independent practice	5 min

In addition to attending weekly, guided, online, group singing sessions, participants will be given music CDs, with repertoire and exercises from the guided group singing sessions, to utilise regularly at home. Control arm participants will receive standard care for 12 weeks, with the option to enroll in 12 weeks of guided, online, group singing at the completion of the study period (no data will be collected during this optional period). Participants and their carers will be contacted at 4-week intervals to collect study assessments. The intervention may be discontinued at any time at the participants request or if the site principal investigator deems a participant too unwell to continue. Data will be collected and stored on a REDcap server which is at least as secure as the source. Data will be accessible only by authorised members of the study team and will be stored in accordance with relevant local policies and guidelines to ensure confidentiality.

### Aims and outcomes

Phase II of the trial aims to determine the feasibility and acceptability of guided, online group singing and will collect preliminary data on effectiveness. The primary outcome of feasibility and acceptability will be assessed by the number of participants (and optional carers) that can be recruited, enrolled, and who complete the study within a six-month period (Table 2). Completion will be defined as attendance at a minimum of eight out of 12 sessions over a 12-week period for the intervention arm and completion of the 12-week assessment for the control arm.

**Table 2 Tab2:** Phase II and III primary and secondary outcomes

PHASE II		
Primary outcome	Timepoint	Detail
Feasibility and acceptability	6 months	Number of participants enrolled, randomised, and who complete the program. Completion is defined as attending 8 of 12 singing sessions or completing the week 12 assessment for control arm participants
PHASE III		
Primary outcome	Timepoint	Detail
Quality of life	12 weeks	Between arm difference in SF-36
Secondary outcome	Timepoint	Detail
Anxiety and depression	12 weeks	Between arm difference in HADS
Breathlessness	12 weeks	Between arm difference in Dypnoea-12
Mastery of breathing	12 weeks	Between arm difference in mastery subdomain of CRQ-SAS
Exercise tolerance	12 weeks	Between arm difference in 6MWT
Loneliness	12 weeks	Between arm difference in UCLA-3
Healthcare utilisation	12 weeks	Between arm difference in self-reported healthcare utilisation
Carer quality of life (optional)	12 weeks	Between arm difference in carer SF-36
Patient and carer perceptions of group singing	Baseline, 4-weeks, 12-weeks	Semi-structured interview thematic analysis
Social dynamics and interactions	Throughout intervention	Ethnographic study of group classes

*SF-36* 36-Item Short Form Survey, *HADS* Hospital Anxiety and Depression Scale, *CRQ-SAS* Chronic Respiratory Disease Questionnaire—Self Administered Standardised, *6MWT* 6-Minute Walk Test, *UCLA-3* University of California Los Angeles Loneliness Scale version 3 Short Form

Phase III aims to determine whether guided, online group singing has an effect on quality of life with the primary outcome being between arm difference in quality of life (36-item Short Form Survey (SF-36)) measured at 12 weeks (Table 2) [40]. Secondary outcomes measured using between arm differences at the 12-week timepoint include effects on: anxiety and depression (Hospital Anxiety and Depression Scale (HADS)) [41], breathlessness (Dyspnoea-12) [42], breathlessness mastery (Chronic Respiratory Disease Questionnaire—Self Administered Standardised mastery subdomain (CRQ-SAS)) [43, 44], exercise tolerance (6 Minute Walk Test (6MWT)) [45], loneliness (University of California Los Angeles Loneliness Scale version 3 Short Form (UCLA-3)) [46], healthcare utilisation (self-report), carer quality of life (SF-36, optional), patient and carer perceptions of group singing (thematic analysis of semi-structured interviews) [47], and social dynamics and interactions (ethnographic observation) [48]. We hypothesise that 12 weeks of online, guided group singing will improve health-related quality of life relative to baseline compared to usual care.

Online, group singing sessions will be attended and/or recorded and reviewed by a member of the study team to conduct ethnographic analyses on the interactions between patients, carers, and singing instructors. Additionally, a purposive sample of up to 15 participants from ILD, COPD, and carer groups will be recruited for semi-structured interviews before, during, and after the intervention period to investigate perceptions of the guided, online, group singing intervention. A related ethics approval has been obtained to allow interviews with eligible participants who elect not to continue with the main study (St Vincents Hospital Melbourne HREC, LRR 111.21).

### Sample size

No formal power calculation was performed for phase II. Participant numbers will be assessed at 6-months to determine feasibility of phase III. For phase III, given a minimally clinically relevant difference in SF-36 of 10 points (SD 16) [31, 35] and assuming 80% power and 5% significance level, at least 42 participants per arm are required. To account for 40% attrition rate, at least 140 participants will be recruited. Due to the rolling nature of the singing groups, the clustering effect is assumed to be minimal, therefore no adjustment for clustering has been performed.

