### Treatment allocation

Treatment allocation will be in 1:1 ratio. A randomisation sequence will be developed by the trial statistician who is not involved in recruitment using permuted block design using Stata software [39], stratified by disease type (COPD vs ILD). No trial investigators or personnel will have access to the allocation sequence.

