### Statistical analyses

Phase II feasibility and acceptability outcomes will be analysed descriptively. Outcomes from phase II will inform the delivery of phase III. Phase III primary and secondary outcomes will be analysed on intention-to-treat basis using mixed effect linear regression. Participants will be entered as random coefficients, while time, treatment arm and an interaction between them will be entered as fixed terms. Residuals will be visually inspected and if the model is of poor fit, the outcome will be transformed using natural logarithms. The primary outcome will be expressed as the difference in SF-36 at 12 weeks with 95% confidence intervals. If the model remains of poor fit despite the outcome transformation, then mixed effect ordinal logistic model will be used and results will be expressed as odds ratios with 95% confidence intervals. Additional per protocol analysis will be performed using a subgroup of participants who have completed the last visit and have completed at least 8 sessions over 12 weeks.

Multiple exploratory subgroup analyses will be performed, including: sex (female vs male), age group (60 years, 60–70 years, or > 70 years), disease severity (mild-moderate vs severe), disease type (COPD vs ILD), prior psychological disease (present vs absent), breathlessness (mMRC of 2 vs 3 vs 4), and previous pulmonary rehabilitation (yes vs no). Subgroup analysis will be performed by including an interaction term between subgroup and treatment arm in the initial model. Additional analysis will involve the associations between change in the outcome and compliance to intervention and presence of carer in group sessions. These will be performed using linear regression. Outcomes are collected at multiple time-points throughout the study to allow for better missing data imputation, which will be performed within the mixed effects model (using maximum likelihood estimation).

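### Clustering by singing group is set to zero on the strength of rolling entry alone, so 80% power at 42 analysed per arm is an upper bound and the primary standard error is understated for any positive intra-group correlation

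*Protocol article*

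**What the plan says.** The Sample size section of the protocol article plans phase III for a 10-point difference in SF-36 with SD 16, "assuming 80% power and 5% significance level", and concludes that "at least 42 participants per arm are required". It then adds: "To account for 40% attrition rate, at least 140 participants will be recruited". On grouping, it reasons from the rolling nature of the singing groups that "the clustering effect is assumed to be minimal, therefore no adjustment for clustering has been performed". That is the only reason offered, and no ICC is stated.

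Intervention and data collection describes how treatment is delivered: "Enrollment will be on a rolling basis with a maximum of 12 patient participants and 12 carers, with up to two groups running concurrently". Sessions are weekly for 12 weeks, by teleconference, led by a senior music therapist. Controls continue standard care individually.

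Statistical analyses gives the model for the primary and secondary outcomes: "Participants will be entered as random coefficients, while time, treatment arm and an interaction between them will be entered as fixed terms". Singing group does not appear in it.

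**The concern.** Patients who share sessions and peers for up to 12 weeks may have outcomes more alike than patients in different groups. Here this can arise in one arm only. If it does, the intervention-arm mean is less precise than the mean of the same number of independent patients. A model with only a participant random term accounts for repeated measures on a patient but not for similarity between patients of the same group.

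The protocol gives some reason not to take the correlation as nil. Its Discussion notes that benefits of group singing have been attributed in part to social connection, and its outcomes include loneliness and the social dynamics of the classes.

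Two things are at stake. One is the planned power. The other is the validity of the primary 95% confidence interval and test, because the error runs in the anti-conservative direction and a positive result could be challenged on that ground.

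**Working it through.** **Inputs.** Difference 10, SD 16, 42 analysed per arm, 40% attrition and 140 recruited (Sample size); 1:1 allocation (Treatment allocation); at most 12 patients per group (Intervention and data collection). Sidedness is not stated. Two-sided is inferred, because a one-sided 5% test would need only 32 per arm. The ICC is not stated; 0.01, 0.05 and 0.10 are assumed for illustration.

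**The plan's own figures.** The normal approximation gives n = 2 × [16 × (1.96 + 0.84)/10]² ≈ 40.2, so 41 per arm. The noncentral t calculation gives 79.8% power at 41 and 80.8% at 42, so 42 per arm. Recruitment is 84/0.6 = 140. Both stated numbers reproduce, with clustering at zero.

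**Group size analysed.** A full group of 12 with 40% attrition leaves 12 × 0.6 = 7.2, taken as m = 7. That makes 42/7 = 6 groups.

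**Clustering in the intervention arm only.**

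- Design effect: DEFF = 1 + (m − 1) × ICC
- True SE = 16 × √(DEFF/42 + 1/42)
- SE ignoring groups = 16 × √(2/42) = 3.49
- Power (normal) = Φ(10/SE − 1.96)
- Power (t) = noncentral t with 82 df
- Type I error ignoring groups = 2 × [1 − Φ(1.96 × 3.49/SE)]

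Example at ICC 0.05: DEFF = 1 + 6 × 0.05 = 1.30; SE = 16 × √(2.30/42) = 3.74; power = Φ(10/3.74 − 1.96) = 76%; type I error = 2 × [1 − Φ(1.83)] ≈ 6.8%.

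| ICC (assumed) | DEFF | SE | Power, normal | Power, t | Type I error |
|---|---|---|---|---|---|
| 0 | 1.00 | 3.49 | 81.7% | 80.8% | 5.0% |
| 0.01 | 1.06 | 3.54 | 80.6% | 79.6% | 5.3% |
| 0.05 | 1.30 | 3.74 | 76.1% | 75.2% | 6.8% |
| 0.10 | 1.60 | 3.98 | 71.0% | 69.9% | 8.6% |

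Coverage of a nominal 95% interval is 100% minus the last column. A simulation of a t-test ignoring six groups of 7 (40,000 replicates) gave type I errors of 5.3%, 6.6% and 8.3% at the three positive ICCs.

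**Few groups.** With six groups, Satterthwaite-type degrees of freedom are df = (v₁ + v₀)²/[v₁²/(6 − 1) + v₀²/41], where v₁ = DEFF/42 and v₀ = 1/42. At ICC 0.05 this gives about 14.6 df and power of about 70%.

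**How far rolling entry dilutes this.** Suppose instead two continuing groups, each contributing 21 analysed patients, with start dates uniform over T weeks and correlation proportional to the share of the 12 weeks that two patients overlap. Mean overlap is a − a²/3 with a = 12/T. For T = 40 weeks it is 27%. For T = 66 weeks (24 months less six for phase II, 78 weeks, less the last 12-week course) it is 17%. At ICC 0.05, DEFF = 1 + 20 × 0.05 × overlap = 1.27 to 1.17, with normal-approximation power of 77% to 78.5% and type I error of 6.6% to 6.0%. The effect is smaller than in the table but not zero.

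**The case against.** The assumption is disclosed, the arithmetic is right given it, and the size of any harm depends on an ICC that the documents do not supply. At ICC 0.01 the loss is about one point of power and 0.3 points of type I error, which fits the authors' description of clustering as minimal. All of this stands: the defect is an unsupported assumption, not a miscalculation.

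Other points also stand in part. Rolling entry does dilute the correlation. A therapist common to all groups adds no variance between groups, and a benefit shared equally by every group is a treatment effect, not an ICC. The Discussion itself doubts whether online delivery can create comparable connection. The type I figures need group effects that differ while averaging to zero. The article condenses a fuller protocol, so a group term might exist elsewhere; but the article states the decision, its reason and a model consistent with it, which is more than silence.

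Two stronger readings are tempting and not supported:

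- **Two fixed clusters of 21.** A reader might treat the two concurrent groups as two permanent clusters with a constant ICC, which at ICC 0.05 gives about 65% power and 11% type I error. With at most 12 patients enrolled and a 12-week course, many of those 21 would never share a session.
- **Twelve analysed per group with 42 per arm.** At ICC 0.05 this gives about 72% power and 8.3% type I error, but full groups of 12 sit badly with 42 analysed after 40% attrition. If all 70 per arm were analysed in groups of 12, normal-approximation power would be 90.6% at ICC 0.05. The 8.3% type I error would remain, so low attrition cures the power problem but not the inference problem.

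**Conclusion.** The point holds as an unsupported assumption carried into both the sample size and the described analysis. For any positive ICC the standard error of the primary comparison is understated, and the stated 80% power at 42 analysed per arm is an upper bound. With about 7 analysed per group, the plausible loss runs from about one power point (ICC 0.01) to about 11 (ICC 0.10), before any allowance for few groups. The direction is certain for a positive ICC; the size is not, because the ICC is assumed. The documents do not support saying that the trial is badly underpowered or that its type I error is known to exceed 5%.

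**What to change.** 1. Record the singing group and the sessions each intervention participant attended.
2. Before unblinding, prespecify a singing-group random effect in the intervention arm only, with small-sample degrees of freedom (Satterthwaite or Kenward-Roger). At minimum, prespecify it as a sensitivity analysis of the primary outcome.
3. State the rule that assigns rolling entrants to groups, and repeat the analysis under an alternative rule. Any fixed cut, such as 12-week intake blocks, is partly arbitrary because patients overlap across it.
4. Report the estimated ICC with its uncertainty.
5. In Sample size, replace the assumption of minimal clustering with power stated over ICC 0 to 0.10 at the unchanged sample size.

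The cost is analysis-plan wording and one more item of data capture; no extra patients are needed. The downsides are a wider confidence interval, a lower quoted power, and a group variance that about six groups will estimate imprecisely.
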